**Medical costs (for both intervention and control arm)**				
Inpatient cost	Time, human resources, facilities used for inpatient care	Mean days of stay and frequency of hospitalization within trial period	Mean cost replacement value recorded in social medical scheme	Reimbursement system
Outpatient cost	Time spent in delivering care	Number of follow-up visits	Replacement value converted to annual equivalent cost	(Estimated)
Medication cost	Self-reported medication use	Number of medications used and adherence rate	Replacement value converted to annual equivalent cost based on local medication price list	Follow-up survey

#### Resources used to support program delivery

Program costs are captured based on a detailed inventory of all resources that are used to support the design and delivery of the SINEMA program. This consists of the administrative cost of headcounts of local project manager and printing materials, the cash support that compensates for the time and efforts of the village doctors, township physicians, and county physicians in delivering the SINEMA intervention over the trial period, and the resources used for maintaining the digital component of the SINEMA intervention (including daily voice messages to patients, the mobile application server, and labor cost related to system maintenance).

#### Resources used for healthcare services

Medical costs are measured mainly by estimating the direct medical cost with individual-level data, including both inpatient costs and outpatient costs for medications. Inpatient costs during the trial period among all participants were retrospectively collected from the urban and rural resident basic medical insurance system from four major key hospitals in the region. A list of medical conditions, including cardiovascular or cerebrovascular events, or other cardiometabolic-related health conditions, is generated by researchers. All relevant inpatient records that matched the conditions will be included in the analysis and total costs will be used in the analysis. Outpatient costs were estimated by the number of hospital visits and medication use. Medication costs will be valued based on the general essential medication list and the standard unit cost for each type of medication as the “zero markups” regulation requires no additional costs on medications in the primary care settings (14).

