#### Health state utility

Health state utility (HSU) estimations will be derived from self-reported health-related quality of life (HRQoL) which was measured using the Chinese version of the EQ-5D-5L, a broadly used generic multi-attribute health utility instrument (15) at baseline and 1-year follow-up. For assessing HRQoL, study data collectors who were staff from the Center of Disease Prevention and Control in the nearby county read out the questionnaire and items for participants and collected the data. After answering the questions for EQ-5D, participants were asked to point out the health score by fingers on a paper version of the EQ-Visual Analog Scale, and then, the data collectors entered the responded values into the online survey platform. An HSU was calculated for each respondent by using the Chinese version of population-based preference weights (16), which ranged from −0.391 to 1, with 1 representing the value of full health, 0 representing deaths, and −0.391 representing the worst state.

Stroke recurrence, hospitalization, disability, and all-cause mortality were measured by using questionnaires at one-year follow-up. Medical and deaths records were also extracted from four major hospitals in the region. These data provide information about the status and trajectory of stroke during the trial period.

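### Inpatient cost counts only admissions on a cardiometabolic condition list, while QALYs have no cause limit, and no planned sensitivity analysis tests what that leaves out

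*Protocol article*

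**What the plan says.** Under Resources used for healthcare services, the protocol article first describes the source of the data: "Inpatient costs during the trial period among all participants were retrospectively collected from the urban and rural resident basic medical insurance system", drawn from four hospitals. It then introduces a filter: "A list of medical conditions, including cardiovascular or cerebrovascular events, or other cardiometabolic-related health conditions, is generated by researchers". The rule for the analysis follows: "All relevant inpatient records that matched the conditions will be included in the analysis and total costs will be used in the analysis".

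Table 1, in the block of medical costs for both arms, gives the inpatient quantity as "Mean days of stay and frequency of hospitalization within trial period" and states no restriction by cause.

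On the effect side, the Health state utility section derives utilities from the EQ-5D-5L, described as "a broadly used generic multi-attribute health utility instrument". The scale is anchored "with 1 representing the value of full health, 0 representing deaths, and −0.391 representing the worst state". Neither the instrument nor the value for death is tied to a cause.

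The section on resource use and costs adopts mainly a health sector perspective. Table 2 varies inpatient cost only for admissions to other facilities. The limitations in the Discussion mention the four-hospital restriction and unpaid labour, but not the condition filter.

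**The concern.** An incremental cost per QALY is a coherent ratio when its two parts cover the same events. Here the numerator includes an admission only if its diagnosis is on the list, while the denominator responds to any illness or death.

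A participant admitted for an off-list condition who is left in worse health, or who dies, lowers the QALYs of that arm and adds no inpatient cost to it. An off-list admission that is avoided can raise QALYs with no saving recorded. The declared perspective makes the gap harder to defend, since the healthcare system also bears the cost of off-list admissions.

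At stake is the decision rule in Study design, which compares the cost per QALY with a threshold of 1.5 times gross domestic product per capita. If off-list costs are unbalanced between arms, both the ratio and the acceptability curve move, and no planned analysis would show by how much.

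**Working it through.** The article reports no cost, admission rate or QALY result, so there is no figure to reproduce. The check is a comparison of sections followed by algebra on the article's own ratio.

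**Scope of each component**

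| Component | Place in the protocol article | Limited by cause? |
|---|---|---|
| Inpatient cost, text | Resources used for healthcare services | Yes, list-matched records only |
| Inpatient quantity | Table 1 | No limit stated |
| Utility and death | Health state utility | No |
| Perspective | Resource use and costs | Health sector, no limit by condition |
| Inpatient sensitivity analysis | Table 2 | Other facilities only; no all-cause scenario |

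**Effect on the ratio**

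The Data analysis section defines the ICER as the cost difference divided by the effect difference. Write:

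- ΔC_list = mean cost difference, SINEMA minus usual care, with listed admissions only
- D = mean off-list inpatient cost per participant, SINEMA minus usual care
- ΔQ = incremental QALY

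Then:

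- ICER_list = ΔC_list / ΔQ
- ICER_all = (ΔC_list + D) / ΔQ
- ICER_all − ICER_list = D / ΔQ

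If the mean cost of an off-list admission is the same in both arms, D = (off-list admission rate under SINEMA − rate under usual care) × that mean cost.

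For ΔQ > 0:

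- D > 0: the listed-condition ratio is too low and flatters SINEMA.
- D < 0: the listed-condition ratio is too high and works against SINEMA.
- D = 0: no change.

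**Effect on the decision**

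At threshold λ, the net benefit with listed costs is λΔQ − ΔC_list. With all-cause inpatient cost it is λΔQ − ΔC_list − D. A favourable conclusion is reversed only if D exceeds the listed-condition net benefit. An unfavourable one is reversed only if −D is at least as large as the shortfall.

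**What the documents give for D**

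Nothing. They report neither off-list admissions by arm nor their cost, so both sign and size are unknown.

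**Reach of the mismatch**

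It concerns the cost per QALY. Systolic blood pressure is not an all-cause measure, so the same argument does not apply to the cost per mmHg. Utility is measured only at baseline and one year. An off-list admission is therefore likely to show in the QALYs only if its effect lasts to the one-year assessment or it ends in death.

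**The case against.** The strongest defence is that the restriction is stated openly, applies identically to both arms, and fits the stated aim of valuing key resource impacts. Limiting cost to related conditions removes noise from unrelated admissions in a 12-month study. This stands as an argument about the base case: whether listed or all-cause cost should lead is a debatable trade-off. It does not explain why the restriction goes untested. Applying the same rule to both arms prevents bias only if off-list costs are equal between them.

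The word introducing the conditions may also mean that the list is wider than the groups named, which would narrow the gap. Table 1 may simply be shorthand. Both are possible, and both are reasons to reconcile the text.

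Three stronger readings are tempting but unsupported:

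- **That the list was drawn up once results were known.** The Introduction shows that trial results, including hospitalisation, had been reported when the article was written. No section dates the list. The article's silence on masking is a detail that a condensed article may leave to the full protocol.
- **That the filter leaves out harms and so favours SINEMA.** The documents name no off-list harm, and any harm within a listed category is counted. If off-list admissions also fell under SINEMA, the filter works against it.
- **That the reported 35–55% relative reduction gives the size of the listed saving.** That range spans recurrence, hospitalisation, disability and death. It is not a range for inpatient cost.

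Nor does the statement "Stroke recurrence, hospitalization, disability, and all-cause mortality were measured by using questionnaires at one-year follow-up" define the QALY. It describes questionnaire outcomes. The case for an unrestricted denominator rests on the generic instrument and the value of 0 for death.

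**Conclusion.** The point holds in a direction-neutral form. The protocol article fixes a condition-limited inpatient cost, divides it by a QALY difference with no cause limit under a health sector perspective, and plans no analysis to show whether this matters. The resulting error in the cost per QALY is D / ΔQ, which can have either sign and is zero if off-list inpatient costs are balanced between arms.

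Its size cannot be given from the documents. The conclusion rests on the list excluding some admissions, as the wording of the rule implies, and on the health sector perspective being meant to include their cost. It is a modest defect: an untested assumption in the base case and a loose match between Table 1 and the text. It is not evidence that the result will be wrong.

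**What to change.** 1. Add a row to Table 2: the base case remains inpatient cost for listed conditions, and the alternative is all-cause inpatient cost from the insurance records collected for all participants. Report the cost per QALY, the scatterplot and the acceptability curve for both, side by side.
2. Reconcile Table 1 with Resources used for healthcare services, so that days of stay and hospitalisation frequency carry the same restriction as the costs, or are stated to be all-cause.
3. Match records to the list with trial arm masked. This is an inexpensive safeguard, not a remedy for any fault shown in the documents.

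The cost is small if the extraction kept every admission. The text reads as though costs were collected for all participants and then filtered, but it does not say outright that records for all diagnoses were retained. If they were not, a further extraction would be needed, or the restriction should be listed as a limitation. The all-cause result will probably have somewhat wider intervals, which is a reason to present it beside the listed-condition result rather than in its place.

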### Data analysis

The data analyses will be performed using STATA software (StataCorp. 2019. State Statistical Software: Release 16. College Station, TX: StataCorp. LLC). For the within-trial cost-effectiveness analysis, two incremental cost-effectiveness ratios (ICERs) will be calculated to evaluate the incremental cost per QALY and the incremental cost per 1 mmHg reduction in systolic blood pressure.

The ICER formula is given below:

$$\begin{array}{l} ICER=\frac{\;Cost_{SINEMA}-Cost_{Usual\;care}}{Effect_{SINEMA}\;-Effect_{Usual\;care}\;} \end{array}$$

Multivariable or multilevel models (with levels defined as villages considering the cluster design) will be employed to explore factors associated with health resource use, cost, and effectiveness. Generalized linear regression modeling of costs with gamma distributions and log linked for multivariable analyses that adjust for age, gender, stroke type, and length of stay will be performed.

Several sensitivity analyses will be considered to quantify the level of decision uncertainty. Deterministic sensitivity analyses will be performed on chosen variables to identify key determinants for the results, as presented in Table 2. We will generate cost-effectiveness scatterplots to explore the uncertainties around incremental costs and effectiveness. A cost-effectiveness acceptability curve (CEAC) will be created to explore the probabilities of the SINEMA intervention being cost-effective at a range of cost-effectiveness thresholds.

**Table 2 T2:** Sensitive analysis of key indicators.

	**Base case**	**Range**

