## Introduction

Stroke is one of the rising public health challenges worldwide. In 2019, there were ~12 million incident cases of stroke, of which 32.8% were in China (1). Although the stroke incidence rate is increasing, the stroke mortality rate has been decreasing over the past few decades, resulting in a huge number of stroke survivors globally (2). As these stroke survivors need continuous health management and risk control, the spending on post-stroke care causes an economic burden (3). The financial burden of stroke in rural areas is extremely severe (4, 5). As in many undeveloped areas, primary care lacks the capacity to provide guideline-based essential care to stroke patients, and community-based management for secondary prevention of stroke is far from adequate (6). Therefore, it is necessary to emphasize the prevention of recurrent strokes in the rural setting.

The system-integrated and technology-enabled model of care (SINEMA) study was designed to empower both stroke survivors and primary healthcare providers for secondary stroke prevention by training and incorporating both provider-facing and patient-facing mHealth technologies. The effectiveness of the SINEMA model has been evaluated and proven through a two-arm cluster-randomized controlled trial conducted in 50 rural villages of Hebei province in northern China (7). During the 1-year intervention, a statistically significant greater reduction in systolic blood pressure (SBP) was observed in the intervention arm compared with the control arm. Improvement in a few secondary outcomes including a 35–55% relative reduction in stroke recurrence, hospitalization, disability, and death has also been reported, which indicates the great potential benefits of the SINEMA intervention on secondary stroke prevention (8).

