## Materials and methods

### Study design

The economic evaluation is a nested study based on the SINEMA trial, a cluster-randomized controlled trial implemented in 50 villages in rural China. A detailed description of the SINEMA program and intervention design can be found in previous publications (7, 10–12). The economic evaluation will involve a within-trial cost-effectiveness analysis and cost-utility analysis with a 12-month time horizon equal to the follow-up period of the trial. We will calculate the incremental cost-effectiveness ratio in terms of the incremental cost per 1 mmHg change in systolic blood pressure, which is the primary outcome of the trial. In addition, we will also conduct a cost-utility analysis to calculate the incremental cost per quality-adjusted life year (QALY). The SINEMA intervention is deemed as cost-effective if the incremental cost per QALY is no greater than the cost-effective threshold. Following previous research (13), we will adopt the conventional approach by considering the benchmark as 1.5 times of gross domestic product per capita.

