**Effectiveness**		
SBP outcomes	Mean value in change with fully adjustment model	95% confidence interval for non-adjusted and fully adjusted
QALY outcomes	Mean value in change with fully adjustment model	95% confidence interval for non-adjusted and fully adjusted

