**Cost**		
Compensation for village doctors	Recorded headcount cost	Fidelity rate of follow-up visits ranging from lowest value to 100%
Missing information of inpatient care for those who were hospitalized in other healthcare facilities.	Median inpatient cost for same or similar diagnosis	25%, 75% percentile of inpatient cost for those who were hospitalized with same or similar diagnosis.
Missing information of outpatient cost which is not covered by health insurance.	Mean outpatient cost for same or similar diagnosis	25%, 75% percentile of outpatient cost for those who were hospitalized with same or similar diagnosis.
Missing information on medication cost of daily doses.	Mean cost for the conventional drugs	25%, 75% percentile of medication cost for those who took same or similar drugs.
Development cost of the digital health system	None	Development costs of the SINEMA model when the cost was shared by years of follow-up

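### Village clustering is optional and tied to exploratory models, so the plan for this 50-village cluster trial permits cost-effectiveness uncertainty that is too narrow

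*Protocol article*

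**What the plan says.** Study design describes the parent study as "a cluster-randomized controlled trial implemented in 50 villages in rural China", and the Introduction adds that it had two arms. The village is therefore the unit of randomisation.

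In Data analysis, villages appear as a model level in one sentence: "Multivariable or multilevel models (with levels defined as villages considering the cluster design) will be employed to explore factors associated with health resource use". The sentence continues to cost and effectiveness, so it covers both components of an ICER. The next sentence gives the one cost model that is spelled out: "Generalized linear regression modeling of costs with gamma distributions and log linked for multivariable analyses that adjust for age, gender, stroke type, and length of" (the last covariate is length of stay). It names no village term and no clustered standard error.

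The decision outputs are set out separately. The article states that "two incremental cost-effectiveness ratios (ICERs) will be calculated to evaluate the incremental cost per QALY and the incremental cost per 1 mmHg reduction" and defines the ICER as a ratio of differences. On uncertainty it says: "We will generate cost-effectiveness scatterplots to explore the uncertainties around incremental costs and effectiveness", followed by a cost-effectiveness acceptability curve (CEAC). Table 2 gives the base case for both effect measures as "Mean value in change with fully adjustment model", with 95% confidence intervals as the range. None of these places mentions villages.

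**The concern.** Two features of the modelling sentence are a problem. It offers multivariable and multilevel models as alternatives, so a single-level model is an allowed reading. Its stated purpose is to look for associated factors, which is a different task from estimating incremental cost and incremental effect by arm.

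An analyst could follow the section to the letter, fit the gamma GLM with ordinary standard errors, bootstrap individual participants for the scatterplot and CEAC, and be compliant. Within-village correlation is plausible here. Village doctors deliver the intervention, and Table 1 quantifies their cost by the number of villages and by fidelity, so part of the cost is shared within a village. If that correlation is ignored, the intervals are too short and the CEAC is too steep. The article presents the sensitivity analyses, CEAC included, as its account of decision uncertainty for policymakers.

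**Working it through.** **Textual check.** Each place in the article where clustering could be made binding:

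- Modelling sentence in Data analysis: villages named, but as one of two options and for exploring factors.
- Gamma GLM for costs: no village term, no clustered standard error.
- ICER formula: a definition only; the estimator of each increment is not given.
- Scatterplots and CEAC: no method given, clustered or otherwise.
- Table 2 confidence intervals: the adjusted model is not defined, so whether it includes village is unknown.

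No other section makes clustering mandatory.

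**Size.** The article gives no sample size, participants per village, SD or ICC, so there is no figure of its own to reproduce. Assumptions: *m* = 15 to 30 participants per village, equal village sizes, ICC = 0.01 to 0.05, and an analysis that ignores villages completely.

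Formulas:

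- Design effect: DE = 1 + (*m* − 1) × ICC
- Understatement of the standard error: √DE
- True coverage of a nominal 95% interval: 2Φ(1.96/√DE) − 1

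| *m* | ICC | DE | √DE | Coverage |
|---|---|---|---|---|
| 15 | 0.01 | 1 + 14 × 0.01 = 1.14 | 1.07 | 93% |
| 30 | 0.01 | 1 + 29 × 0.01 = 1.29 | 1.14 | 92% |
| 25 | 0.05 | 1 + 24 × 0.05 = 2.20 | 1.48 | 81% |
| 30 | 0.05 | 1 + 29 × 0.05 = 2.45 | 1.57 | 79% |

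**Effect on the CEAC.** With approximately normal net benefit, a naive probability *p* becomes Φ(z_p/√DE). At *m* = 25 and ICC 0.05, a naive 0.95 becomes Φ(1.645/1.483) = 0.87, and a naive 0.975 becomes Φ(1.96/1.483) = 0.91. At *m* = 25 and ICC 0.01, where √DE = 1.114, a naive 0.95 becomes 0.93.

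**Simulation check.** Assumed 25 villages per arm (the article does not give the split), 25 participants per village, outcome SD 1. The village bootstrap resampled whole villages within arm.

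| ICC | True SE | Individual bootstrap | Village bootstrap |
|---|---|---|---|
| 0.02 | 0.071 | 0.056 | 0.068 |
| 0.05 | 0.083 | 0.057 | 0.080 |

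Resampling individuals gives nearly the same SE whatever the ICC. Resampling villages comes close to the true SE.

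**The case against.** The strongest defence is that the article does recognise the cluster design, in a sentence that covers both cost and effectiveness, and that a condensed article may leave standard-error and resampling methods to a fuller plan. Part of this stands. The CEAC method is unstated; it is not stated to be non-clustered, and silence alone would be no finding. What remains is that the article does address clustering, and does so in terms that make it optional and exploratory.

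It can also be said that the adjusted effect model in Table 2 may already account for villages, through the parent trial. The article does not settle this either way. If it does, the effect interval is protected, but the cost side and the joint distribution are not.

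A further fair point is that Study design judges cost-effectiveness by comparing the incremental cost per QALY with a threshold of 1.5 times GDP per capita. That rule uses the point estimate, so clustering would usually not change the stated decision.

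A reader might go further and infer from Table 2 that an adjusted effect is divided into unadjusted costs, because one base-case entry reads "Recorded headcount cost", and that the cost-effect correlation is therefore lost. The article does not support this. That entry is a single row, for village-doctor compensation, in a table of inputs to the deterministic sensitivity analysis. Data analysis plans a covariate-adjusted cost model, and no section says how the joint distribution is handled.

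**Conclusion.** The point holds as a weakness in what the plan permits. As worded, it allows an analysis that ignores the unit of randomisation, and for any ICC above zero such an analysis overstates certainty about incremental cost, incremental effect and the probability of cost-effectiveness. The direction is firm. The size is not, because cluster size and ICC are assumed: it runs from minor at the low end of the assumed range to a serious loss of coverage at the high end. Unequal village sizes would generally add to it.

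The harm is to stated uncertainty; the ICER point estimate need not be biased. For that reason, and because the threshold rule uses the point estimate, this should be corrected but is not a fatal flaw.

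**What to change.** In the modelling sentence, delete the words that offer a multivariable model as an alternative. Then state that incremental cost and incremental effect for both ICERs, and their uncertainty, will account for village clustering through village random effects or village-clustered standard errors, including in the gamma GLM. State also whether the adjusted effect model in Table 2 includes village.

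Draw the scatterplots and CEAC from a joint cost-effect analysis that keeps villages intact. A two-stage bootstrap that resamples villages within arm, or a bivariate multilevel model, would each serve; the choice can be left to the analysis plan.

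The cost is a short rewording and modest programming, with no new data. The intervals will be wider and the CEAC flatter.
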